#### 2.3.4. Criteria for withdrawal, dropout, and removal

Participants presenting any of the following situations will be considered as the withdrawal cases: (1) the disease get worse after treatment in this study; (2) complications or severe adverse events (SAEs) occur during the trial; (3) the utilization of related treatments other than the study, which may impact upon the results of this study; (4) poor compliance, or the number of appointments for treatment does not meet the requirements (<80%); (5) unblinding for emergency situations; and (6) participants request to withdraw from the study.

Participants unable to complete the observation procedure of the study, regardless of the reasons, will be classified as dropout cases. The last outcome data of dropout cases will be included in data analysis. During the trial, participants will be removed if (1) they are wrongly enrolled due to misdiagnosis; (2) they do not accept the treatment after being enrolled in the study; (3) they participate in other clinical trials at the same time; and (4) the post-inclusion data is incomplete and there are no evaluable records for the analysis of the results. Data from withdrawal and dropout cases will be included in intention-to-treat analyses.

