### 2.6. Interventions

The ACE operation in this study will be carried out in accordance with the Acupuncture Technical Operation Standard of the People’s Republic of China for ACE. Participants in both groups will accept treatments once every 2 weeks, for an 8-week period. During treatment, participants will be separated in different treatment rooms to avoid communication. Both treatments will be conducted by trained acupuncturists who are qualified, have acupuncture affiliation, and experience in clinical practice for more than 3 years. During the treatment and observation period of the study, if the participant’s pain symptoms worsen, the oral NSAIDs drug celecoxib (Pfizer Pharmaceuticals Ltd.) (Frampton and Keating, 2007; Foster et al., 2018) will be given orally for 2 days at a dose of 200 mg twice daily. If pain remains unrelieved, participants will be withdrawn from the study.

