### 2.7. Outcomes measurement

The efficacy evaluation in this study will include the primary outcome indicator VAS (Bijur et al., 2001). The secondary outcomes are the Roland-Morris Disability questionnaire (RMDQ) (Law et al., 2021), Oswestry Disability Index (ODI) (Mehra et al., 2008), and the Short Form 36-Health Survey (SF-36) (Taft et al., 2004). Safety outcomes will be evaluated by the incidence of adverse event. All evaluation indicators will be assessed at six time points: baseline, mid-treatment (4 weeks of treatment), post-treatment (8 weeks of treatment), and 1 month, 3 months, and 6 months after the treatments. Researchers who do not take responsibility for other processes in the study will be appointed as outcome assessors. Details of the observational items and the time window for data collection are shown in Table 2.

**TABLE 2 T2:** Schedule of enrolment, interventions, and assessments.

	Enrolment and allocation		Treatment period				Follow-up period		
Timpepoint	Screening (−3 to 0 d)	Allocation (0 d)	2 w	4 w	6 w	8 w	1 m	3 m	6 m

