### 2.8. Data collection and management

After the included participants sign the informed consent forms, researchers will collect individual information, such as general demographic information, clinical history, and baseline data for VAS, RMDQ, ODI, and SF-36. Outcome indicators will be measured at the previously indicated six time points, and documented in the CRFs. When the trial is completed, two researchers who are neither involved in the distribution nor the outcome evaluation will independently extract data from CRFs into an Excel table. The statistician will then conduct statistical analysis on this data after double check confirmation. To protect the privacy of participants, personal names will be replaced by numbers combined with initials. Researchers shall maintain data confidentiality for 5 years after the termination of the trial. In order to reduce the dropout rate of participants, researchers will contact the participants by telephone 2 days before their treatments to enquire on their conditions and encourage them to accept the treatments as scheduled.

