### 2.10. Statistical analysis

Statistical analysis will be computed using Statistical Analysis System (SAS) v9.4 by a statistician. Continuous variables subject to normal distribution are expressed as mean ± standard deviation, otherwise they will be expressed as median (interquartile range). Discontinuous variables will be expressed as composition ratio and rate. The baseline comparison of continuous variables will be performed by *t*-test or non-parametric test, and the baseline comparison of discontinuous variables by the chi-squared test. Repeated measures analysis of variance (RM-ANOVA) will be performed on the measurement data at multiple observation time points, to analyze the trend over time and the interaction between treatment times. The statistical significance level will be 0.05 (bilateral) with 95% confidence interval. The safety analysis will mainly be based on descriptive statistics, including the incidence and the specific description of adverse events.

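### Participants whose worsened pain stays unrelieved are withdrawn from the study, and nothing in the article continues their VAS, so later primary-outcome values are lost because of the primary outcome

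*Protocol article*

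**What the plan says.** Section 2.6 (Interventions) sets a rescue rule. It applies "During the treatment and observation period of the study". If pain worsens, celecoxib is given for two days, and then: "If pain remains unrelieved, participants will be withdrawn from the study".

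Section 2.3.4 (Criteria for withdrawal, dropout, and removal) lists as its first withdrawal criterion "the disease get worse after treatment in this study". It does not mention the rescue step. The same section adds two sentences on data use: "The last outcome data of dropout cases will be included in data analysis", and "Data from withdrawal and dropout cases will be included in intention-to-treat analyses".

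The primary outcome is pain on a 10 cm VAS (2.7.1). Section 2.7 and Table 2 schedule it at baseline, weeks 4 and 8, and 1, 3 and 6 months after treatment. Section 2.10 states the analysis: "Repeated measures analysis of variance (RM-ANOVA) will be performed on the measurement data at multiple observation time points".

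**The concern.** The event that removes a participant is a high pain score, or something very close to one, and pain is what the trial measures. Values missing for that reason are not a random subset. If ACE relieves pain, fewer ACE than sham participants should meet the rule, so the loss would be unequal between arms and concentrated in people who are doing badly. The estimated difference then depends on what is assumed about scores that nobody collected. No later analysis can recover a month 6 score that was never taken.

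**Working it through.** **1. Does withdrawal stop the assessments?** Table 2 schedules study treatment up to week 8 and none at months 1, 3 and 6. The rule in 2.6 also applies in the observation period. A participant withdrawn then has no treatment left to stop, so the only thing withdrawal can end is assessment. No section separates stopping treatment from leaving the study.

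**2. Do the data-use sentences repair this?** No. Both concern data that exist. Using a last outcome presupposes that later ones are absent.

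**3. What is lost, from Table 2 (six VAS time points):**
- Withdrawn after the week 4 visit: baseline and week 4 kept, 6 − 2 = 4 lost (week 8, months 1, 3, 6).
- Withdrawn after the week 8 visit: 6 − 3 = 3 lost (months 1, 3, 6).

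No VAS is scheduled at the week 2 and week 6 treatments. For a withdrawal there, it is not fixed whether the triggering score is on record.

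**4. Size at week 8 (illustration).** The plan gives no figure for this. From section 2.5: control mean 4.64, SD s = 1.42, difference 1.02 cm, so the ACE mean is 4.64 − 1.02 = 3.62. Assumed: baseline mean 5.5; week 4 means 5.00 (sham) and 4.49 (ACE); equal SDs; correlation ρ between any two visits; withdrawal at week 4 if VAS exceeds baseline by more than t; recorded week 4 score carried to week 8.

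Let D be the week 4 score minus baseline. It has mean m4 − 5.5 and SD σ = s√(2(1−ρ)). With k = (t − (m4 − 5.5))/σ, the proportion withdrawn is p = 1 − Φ(k). Carrying week 4 forward raises an arm's week 8 mean by

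shift = (m4 − m8)·p + ½·σ·φ(k),

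where ½ is the regression slope of (week 4 − week 8) on D under equal correlations.

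For ρ = 0.5, σ = 1.42:
- t = 0, sham: k = 0.352, p = 0.362, shift = 0.36×0.362 + 0.71×0.375 = 0.397. ACE: k = 0.711, p = 0.238, shift = 0.87×0.238 + 0.71×0.310 = 0.427. Estimate = 1.02 + 0.397 − 0.427 = **0.99 cm**.
- t = 1, sham: k = 1.056, p = 0.145, shift = 0.36×0.145 + 0.71×0.228 = 0.214. ACE: k = 1.415, p = 0.078, shift = 0.87×0.078 + 0.71×0.146 = 0.172. Estimate = 1.02 + 0.214 − 0.172 = **1.06 cm**.

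For ρ = 0.7 the same formula gives about 1.04 cm (t = 0) and 1.07 cm (t = 1). The shift changes sign within plausible inputs. With no true effect the two arms have the same shift, and it cancels.

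**5. Size with the eligibility range imposed (simulation, 41 per arm).** Baseline was kept within 4 to 7 cm (2.3.2), t = 0.5 to 1.5 cm, ρ = 0.3 to 0.7, and the week 4 trigger was recorded and carried forward.

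| Celecoxib relieves | Estimate (true 1.02 cm) | Withdrawn by week 8, central case (t = 1.0, ρ = 0.5) |
|---|---|---|
| no one | 1.05 to 1.10 | 16.8% sham, 6.5% ACE |
| half | 1.04 to 1.06 | 8.9% sham, 3.3% ACE |

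If exits also occur at weeks 2 and 6 and only scheduled scores are kept, the central case gives about 0.96 cm (no one relieved) or 1.00 cm (half relieved). With no true effect, bias was within 0.002 cm and the rejection rate was 0.047 to 0.053.

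**The case against.** Several points on the other side have weight.

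- **The article condenses a fuller protocol.** Visits after withdrawal might be described there. This would answer a complaint about missing detail. It does not answer a stated rule that takes people out of the study during a period when only assessments remain.
- **Section 2.3.4 only labels worsening a withdrawal case.** This stands. A reader might infer that every participant who worsens stops giving VAS scores. The text does not say so: it defines dropout separately as failing to complete observation, and 2.6 puts rescue first. The point therefore rests on 2.6, with 2.3.4 as an unaligned second statement.
- **Some follow-up after withdrawal is stated.** For serious adverse events, 2.7.3 has researchers follow and record the participant's condition. A reader might infer that those withdrawals also end outcome collection. VAS is not named there, but the text does not support that reading, and it is not claimed here.
- **Section 2.5 allows for 20% loss.** This covers numbers lost. It does not cover loss that depends on the outcome and differs by arm.
- **Scores after withdrawal would include the effect of other treatment.** True, and it is a genuine cost of continued follow-up. But 2.3.4 already commits to including withdrawals in the intention-to-treat analysis, and that aim is better served by observed scores than by carried ones.
- **The illustrated shift is small and rests on assumed inputs, and the check is a week 8 comparison, not the planned RM-ANOVA.** Also true. It limits the size of the claim but not the case for an inexpensive change.

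**Conclusion.** The point holds as a weakness in a stated conduct rule. Participants with unrelieved pain leave the study because of the primary outcome, and 4 or 3 of 6 VAS time points are lost after withdrawal at week 4 or week 8. If ACE works, the loss is likely to be unequal between arms and can distort the effect estimate.

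The size is modest where it could be illustrated. At week 8 the estimate lies between about 0.96 and 1.10 cm against 1.02 cm, a shift of −0.06 to +0.08 cm. This rests on an assumed worsening threshold, visit correlation, response to celecoxib, baseline distribution and carry-forward of the last score. Exits accumulate through month 6, so later visits could be affected more; they are not quantified here. No power figure is offered, because it depends on when exits occur.

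Two stronger readings are not supported. A reader might infer that the rule inflates false positives; with no true effect the arms lose the same values and there is no bias. A reader might also infer that it exaggerates, or hides, the benefit of ACE; the documents do not fix the direction.

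**What to change.** - In 2.6, replace withdrawal from the study with stopping study treatment.
- Continue VAS, RMDQ, ODI, SF-36 and adverse event assessments at all scheduled visits, by telephone where needed, unless the participant withdraws consent for follow-up.
- Analyse these data in the allocated group.
- Make the first criterion in 2.3.4 refer to the rescue rule in 2.6, so that one sequence applies.

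Cost: a protocol amendment (2.1 gives the route through the ethics committee) and the remaining visits or calls for a few people. In the central illustration that is 41×0.168 ≈ 7 sham and 41×0.065 ≈ 3 ACE participants if celecoxib relieves no one, and about 4 and 1 if it relieves half (41×0.089 and 41×0.033). Telephone contact is already in use: "researchers will contact the participants by telephone 2 days before their treatments". Rescue and decisions to stop treatment do not change. The downside is that some scores after withdrawal will reflect other treatment, which should be recorded and reported alongside them.

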### 2.5. Sample size

The VAS score is the primary outcome indicator for this trial. Based on the results of the pre-test, it is known that the VAS score in the control group was 4.64 ± 1.42 cm and is expected to be reduced by 1.02 cm after treatment with ACE, setting a two-sided test with α = 0.05, β = 0.10. A sample size of 34 cases per group was calculated using PASS 15 software. Considering the 20% lost to follow-up calculation, the final number of cases needed for at least two groups was 41, for a total of at least 82 participants included.

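### The last-value rule for dropouts reads most naturally as last observation carried forward, which can shift the VAS difference in either direction

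*Protocol article*

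**What the plan says.** Section 2.3.4 defines the group broadly: "Participants unable to complete the observation procedure of the study, regardless of the reasons, will be classified as dropout cases". The rule for their data follows: "The last outcome data of dropout cases will be included in data analysis". The section closes with "Data from withdrawal and dropout cases will be included in intention-to-treat analyses".

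Section 2.10 gives the analysis of repeated outcomes: "Repeated measures analysis of variance (RM-ANOVA) will be performed on the measurement data at multiple observation time points". Section 2.7 sets six assessments: baseline, weeks 4 and 8, and 1, 3 and 6 months after treatment. Section 2.5 states that "The VAS score is the primary outcome indicator for this trial" and allows for loss: "Considering the 20% lost to follow-up calculation".

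Two rules tie leaving the study to the primary outcome. Section 2.3.4 lists among the withdrawal reasons "the disease get worse after treatment in this study". Section 2.6 adds, for pain that persists after rescue medication, "If pain remains unrelieved, participants will be withdrawn from the study".

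**The concern.** The last-value sentence is the only rule in the article on what a dropout contributes to the analysis, so this is a stated method and not a detail left out. If it means LOCF, a patient lost after the week-4 visit contributes the week-4 VAS as the week-8 value and as every later value.

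That is hard to defend here for two reasons. First, VAS is expected to fall during treatment and may move again in follow-up, so an early value is a poor stand-in for a later one. Second, patients who worsen are withdrawn. Their last scheduled VAS may have been taken before the worsening, and the carried value can then look better than their true state.

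At stake is the primary estimate. LOCF is not reliably conservative: the direction of its error depends on which arm loses more patients and when. Carrying week 8 forward would also flatten the follow-up course that the RM-ANOVA is meant to describe.

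**Working it through.** **1. Is it LOCF?** The term does not appear in the article. Classical RM-ANOVA needs a value at every time point for each patient. If dropouts are to be in an intention-to-treat RM-ANOVA through their last outcome, the natural way is to fill later visits with it. If the sentence means only that collected data are kept, a classical RM-ANOVA would leave incomplete patients out, against the intention-to-treat sentence; only a model that accepts incomplete records would fit that reading.

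**2. How many patients?** The planned 41 per arm is 34 × 1.20 = 40.8, rounded up. Twenty per cent of 41 is 8.2, so up to about 8 per arm would carry a value at week 8. This is an upper bound: the 20% is not dated, and anyone lost after week 8 has an observed week-8 value. (The 34 does not itself follow from a two-sided 0.05 test with 90% power, for which the normal formula gives 41. That is a separate matter and is not used here.)

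**3. Expected week-8 difference under LOCF.**

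From Section 2.5: control mean 4.64, ACE mean 4.64 − 1.02 = 3.62, SD 1.42. Assumed: these are week-8 means; baseline mean 5.5 (midpoint of the entry range, above 4 and below 7 cm); linear change to week 8; all loss before week 8; loss unrelated to pain; the loss splits between arms.

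Week-4 means are then (5.5 + 4.64)/2 = 5.07 for sham and (5.5 + 3.62)/2 = 4.56 for ACE. Let pS and pA be the proportions lost. The difference is sham minus ACE, so positive values favour ACE.

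- Week 4 carried: 1.02 + pS(5.07 − 4.64) − pA(4.56 − 3.62) = 1.02 + 0.43 pS − 0.94 pA
- Baseline carried: 1.02 + 0.86 pS − 1.88 pA
- No true effect (both arms as sham): 0.43(pS − pA) with week 4 carried, 0.86(pS − pA) with baseline carried

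| Loss ACE/sham | True 1.02, week 4 carried | True 1.02, baseline carried | True 0, week 4 carried | True 0, baseline carried |
|---|---|---|---|---|
| 20%/20% | 0.918 | 0.816 | 0 | 0 |
| 30%/10% | 0.781 | 0.542 | −0.086 | −0.172 |
| 10%/30% | 1.055 | 1.090 | 0.086 | 0.172 |

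**4. Simulation check.** This used 41 per arm, 4,000 runs, an assumed correlation of 0.6 between adjacent visits, week 4 carried forward and a two-group comparison at week 8.

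- Loss unrelated to pain, true 1.02: 0.92 (20%/20%), 0.78 (30%/10%) and 1.05 (10%/30%), matching the table.
- Loss made more likely by high week-4 pain, true 1.02 (splits now nominal): 0.95, 0.78 and 1.12.
- No true effect: about 0 with equal loss, and 0.09 to 0.14 in either direction with unequal loss.
- 95% interval coverage was 0.89 at 30%/10% with a true effect, and 0.93 to 0.95 otherwise. Rejection under no effect was 6.1% to 6.7% with unequal loss and below 5% with equal loss.
- A regression estimator valid under missing at random stayed within about 0.01 of the truth throughout.

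**5. Follow-up illustration.** Assume partial relapse at 6 months to 4.4 (ACE) and 5.0 (sham), a true difference of 0.60, with week 8 carried forward. The expected difference is 0.60 − 0.36 pS + 0.78 pA: 0.684 (20%/20%), 0.570 (10%/30%) and 0.798 (30%/10%). Equal loss, which diluted the effect at week 8, now inflates it.

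**The case against.** The best counter-argument is that the protocol never says values are carried forward or imputed. The sentence may only promise that data recorded before dropout are not thrown away. That reading is possible and cannot be excluded, but it fits poorly with classical RM-ANOVA, and a sentence open to both readings needs rewording in any case.

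A reader might also infer more than the documents support:

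- **That the bias is as large as the baseline-carried figures.** VAS is also taken at week 4, so baseline is the last value only for patients lost before then. Section 2.3.4 further removes patients with no evaluable post-inclusion records, which probably takes out some of these. Those figures are the worst case.
- **That LOCF costs much power.** With baseline carried at 20%/20%, power for 0.816 cm with 41 per arm is about 73%. The fair comparator is not 90%: about 33 observed patients per arm with the full 1.02 cm give about 82%. Carrying week 4 forward (0.92 cm, 41 per arm) gives about 83%. On that basis there is essentially no loss.
- **That standard errors are seriously too small.** Treating carried values as observed is a fault in principle, but in the simulation the coverage loss came mainly from bias, and variance understatement was small with equal loss.
- **That a missing sensitivity analysis is a defect.** This is commonly left to a statistical analysis plan, which is not shown.

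The 30%/10% splits are illustrative, and blinding of participants may keep loss more even. What stands is that the stated rule has an error of unknown sign, in a trial that withdraws patients for worsening pain.

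**Conclusion.** The point holds in this form: the rule most naturally specifies LOCF and can shift the primary VAS difference in either direction. With the week-4 value carried forward, a true 1.02 cm becomes about 0.92, 0.78 or 1.05 depending on how loss splits between the arms. The worst case, baseline carried for every dropout, gives 0.82, 0.54 or 1.09. With no true effect, the spurious difference under unequal loss is about 0.09 cm (0.17 in the worst case); equal loss gives about none.

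These sizes rest on the assumed baseline, the linear course, the loss splits and all loss falling before week 8. They show direction and order of magnitude and do not forecast this trial's bias. The documents do not support calling the trial's result invalid or its type I error badly inflated. They do support replacing the rule, because a better analysis uses the same data.

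**What to change.** Delete the last-value sentence in Section 2.3.4. In Section 2.10, state that the primary VAS analysis is a likelihood-based mixed model for repeated measures, using all observed values from all randomised participants, with no carried-forward values, valid under missing at random. The removal criteria in Section 2.3.4 should be squared with that wording.

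Missing at random may fail where a patient worsens after the last recorded VAS and is then withdrawn. A sensitivity analysis under missing not at random, such as multiple imputation with sham-based or delta-adjusted values for ACE dropouts, is therefore a useful but optional addition.

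The cost is analysis wording, SAS code and slightly more analysis work. Visits, treatment and data collection do not change. Section 2.12 says enrolment is under way, and Section 2.1 asks for a formal, ethics-approved modification where study conduct may be affected, so allow for an amendment and complete it before unblinding.

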### 2.4. Randomization, allocation concealment, and blinding

Eligible participants will be divided randomly into the intervention group (ACE group) or the control group (sham ACE group). The random numbers of allocation sequences will be generated using Statistical Analysis System (version 9.4) by a statistician. Later, the random numbers and groupings will be packaged in opaque and closed envelopes with sequence numbers. The researchers responsible for the participant’s enrolment will take the envelopes with the corresponding number according to the inclusion order, and write down the name, gender, and age of the included participant on the surface of the envelope. All the marked envelopes will be kept by another researcher, who is not involved in participant recruitment.

After the baseline assessment of personal conditions and pre-treatment outcome measurements, acupuncturists will be informed about the different treatments of the participants. The outcome assessors will be blinded to the treatments due to the groups of the participants recorded in the case record forms (CRFs) being replaced by “A” and “B” without details. Additionally, the assessors will also be blinded to recruitment and groupings. All in all, participants, outcome assessors, and statistician in the study will be blinded to the different treatments. Under certain conditions, unblinding will be permissible when participants undergo SAEs or other emergency situations. Once unblinded, participants will withdraw from the trial, and the reasons will be documented and reported by the researchers.

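### The removal rule in Section 2.3.4 implicitly takes some randomised participants out of the set called intention-to-treat, and it overlaps with classes that are kept

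*Protocol article*

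**What the plan says.** Section 2.3.4 sets up three classes.

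- **Withdrawal** has six reasons. They include poor compliance or attendance below 80% (item 4) and the participant's own request (item 6).
- **Dropout** is defined broadly: "Participants unable to complete the observation procedure of the study, regardless of the reasons, will be classified as dropout cases". For these, "The last outcome data of dropout cases will be included in data analysis".
- **Removal** is introduced by "During the trial, participants will be removed if" and has four reasons: wrong enrolment through misdiagnosis (item 1); "they do not accept the treatment after being enrolled in the study" (item 2); "they participate in other clinical trials at the same time" (item 3); and "the post-inclusion data is incomplete and there are no evaluable records for the analysis of the results" (item 4).

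The section then closes: "Data from withdrawal and dropout cases will be included in intention-to-treat analyses". Removed cases are not mentioned there. Section 2.10 names no analysis set, and no other section says that removed cases are kept.

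**The concern.** An ITT analysis takes every randomised participant in the group to which he or she was allocated. A list of who enters the ITT analyses that covers two of three classes, next to a third class described as removed, reads as leaving the third class out. Three of its four reasons can arise after allocation. If such exclusions are related to arm and to outcome, the groups compared are no longer those that randomisation formed, and the result would still carry the ITT label.

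The second problem is that the classes are not mutually exclusive. The same participant can meet the definition of a class that is kept and of the class that is not, and nothing says which prevails. Membership of the primary analysis population then depends on how a case is labelled.

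**Working it through.** **Are removed participants randomised?** Section 2.3.4 speaks of enrolment, not randomisation. Under Section 2.4, however, the enrolling researcher takes the numbered envelopes in order of inclusion. Table 2 puts allocation and the first treatment both on day 0, and removal takes place during the trial. Items 2 to 4 can therefore apply to randomised participants. Item 1 differs in kind: misdiagnosis can in principle be shown from facts that existed before allocation.

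**Do the classes overlap?**

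| Participant | Class that is kept | Removal item |
|---|---|---|
| No record after enrolment | Dropout, whatever the reason | 4 |
| Accepts no session | Withdrawal item 4 (0% attendance is below 80%) or item 6 (own request) | 2 |
| Joins another trial that gives a related treatment | Possibly withdrawal item 3 (outside treatment) | 3 |

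The label matters. As a dropout, a participant with no post-baseline VAS would enter with the last available value, which could only be baseline. As a removal, the same participant would contribute nothing.

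**How large could the effect be?** The plan gives no figure on this point, so there is none to reproduce. From Section 2.5 I take 41 per group and the planned difference of 1.02 cm, with SD 1.42 cm. Two quantities are assumptions: k, the number removed from an arm, and g, the mean VAS of those removed minus the mean of those kept in that arm.

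The mean of the full ACE arm is the mean of those kept plus (k/41) × g, and likewise for sham. The shift of the estimate in favour of ACE is therefore

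bias = (k_ACE/41) × g_ACE − (k_sham/41) × g_sham.

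It is zero if the two terms are equal, or if removal is unrelated to outcome (g = 0 in both arms). With removals in ACE only:

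| k of 41 | g = 1 cm | g = 1.42 cm | g = 2 cm |
|---|---|---|---|
| 1 | 0.024 | 0.035 | 0.049 |
| 4 | 0.098 | 0.139 | 0.195 |
| 8 | 0.195 | 0.277 | 0.390 |

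The extremes are 1/41 × 1 = 0.024 cm and 8/41 × 2 = 0.390 cm, that is 0.024/1.02 = 2.4% and 0.390/1.02 = 38.3% of the planned difference.

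The corresponding two-sided type I error, with no true effect, is Φ(b/SE − 1.96) + Φ(−b/SE − 1.96), where b is the bias and SE = 1.42 × √(1/(41 − k) + 1/41). For k = 4 and g = 1.42, SE = 1.42 × √(1/37 + 1/41) = 0.322, b/SE = 0.139/0.322 = 0.43, and the error is 0.071 instead of 0.05. Over the cells of the table it runs from 0.051 to 0.217.

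Removal of similar participants from sham only gives the same sizes with the opposite sign, against ACE.

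**The case against.** The strongest objection is that exclusion is inferred. The closing sentence does not contain the word only, and the section never says to which set removed cases belong. That stands: a reader might conclude that the protocol declares removed cases excluded from ITT, and it does not. Exclusion is the natural reading, and nothing in the article offers another. A statistical analysis plan, if one exists, might settle the matter. The overlap between classes, however, lies in the text as printed.

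A reader might also infer that ACE, which manipulates the needle to provoke sensation and leaves catgut in the muscle, would lose more of its dissatisfied participants from the analysis. The documents do not support that. Most who leave early, through worsening, adverse events, poor attendance or their own request, are withdrawal cases, which Section 2.3.4 keeps. Refusal before the first session has little route to differ by arm, since participants are blinded and the sham uses the same needle and acupoints. No refusal rates are given. What remains is mainly items 3 and 4, and item 2 where refusal follows a first session.

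Nor does the protocol make removal openly arm-dependent. Section 2.4 blinds participants, assessors and statistician. It also says that "acupuncturists will be informed about the different treatments of the participants", but nowhere are acupuncturists said to decide on removal.

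Finally, a single figure can mislead. Assume that 3 of 41 are removed from ACE only, that those kept average 4.64 − 1.02 = 3.62 cm, and that those removed would have stayed at 5.5 cm. A full-set difference of 4.64 − (38 × 3.62 + 3 × 5.5)/41 = 0.88 cm then appears as 1.02; with 4 removed, 4.64 − (37 × 3.62 + 4 × 5.5)/41 = 0.84 cm does. The counts and the 5.5 cm are assumed. If those removed resembled sham participants at 4.64 cm, three removals would hide only 3 × 1.02/41 = 0.07 cm.

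**Conclusion.** The point holds as a defect of definition. Read as written, Section 2.3.4 implies that randomised participants removed for reasons arising after allocation lie outside the set it calls ITT, and its classes overlap with no rule of precedence.

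Its size is unknown. It may be zero. On the assumption that removal affects one arm only, that 1 to 8 of 41 are removed and that they differ by 1 to 2 cm from those kept, the bias is about 0.02 to 0.39 cm against 1.02 cm planned. The documents do not show that removal would favour ACE or that it would be frequent, and the point does not depend on either.

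**What to change.** Rewrite the paragraph on removal so that it says the following.

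1. The primary (ITT) set is every randomised participant, analysed in the allocated group.
2. Removal items 2 to 4 serve only as reasons for recording that study treatment stopped, or for leaving a per-protocol set. They do not decide membership of the ITT set.
3. Exclusion under item 1 is allowed only if ineligibility is shown by data from before randomisation and judged blind to arm.
4. The withdrawal, dropout and removal classes are reconciled so that each case has one label, or a stated order of precedence.
5. Participants with no post-baseline VAS stay in the set through a pre-stated missing-data method, for example multiple imputation or a longitudinal model with baseline as one of the responses, with a sensitivity analysis. Such participants supply no outcome under any method, so the result for them rests on assumptions. The choice of method is open; stating it beforehand is what matters.

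The cost is a paragraph of wording and one sensitivity analysis; no treatment, visit or measurement changes. The estimate may turn out slightly less favourable. Section 2.12 reports that enrolment is under way, so the change should be made through the amendment route in Section 2.1, before removal decisions accumulate and before unblinding.
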